#### Evaluable cases for primary endpoint

2.5.2

For the purposes of analysis, the study populations are defined in **Table 3**.

**Table 3 T3:** Populations for analysis.

Population	Description
All screened	All participants who sign the informed consent form.
Intent-to-treat (ITT)	All randomized participants whether or not the randomized intervention was administered. This population will be based on the study intervention to which the participant was randomized and will be the primary population for the analysis of efficacy data.
Per-protocol	All randomized participants completing at least two QoL questionnaires 6 months apart, as long as the study participant is disease-free. Participants will be analyzed according to the intervention they actually received.

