### Study design

2.2

This is a multicenter, international, two-arm, randomized (2:1 ratio), open-label, superiority trial, designed to evaluate the proportion of HNC survivors experiencing a clinically meaningful QoL deterioration [reduction of at least 10 points in EORTC QLQ-C30 global health status (13, 14)] between at least 2 visits during post-treatment follow-up (up to 24 months from randomization) with the use of the BD4QoL platform through the web-forms tool for QoL questionnaires answers and through continuous monitoring by a mobile application (App) installed on the study subject’s mobile phone in comparison to those without the BD4QoL platform (SoC). If a clinically relevant deterioration in global health, measured with the EORTC QLQ-C30 global health scale [decrease ≥10 points, as defined in (13, 14)] is detected during the study period, the subject participation in the study will be interrupted (because the aforementioned decrease would imply that the primary endpoint is not met for a specific participant).

Patients will be followed up as per clinical practice (18, 19):

a. All subjects will be asked to complete validated questionnaires [EORTC QLQ-C30 (4), QLQ-HN43 (6), and EQ-5D-5L (7), CBI-B (11)] and PREM on up to 5 occasions over a 2-year period, at randomization (0-month of follow-up), then once every 6 months ± 2 months (after 6, 12, 18, 24 months from randomization).

b. Participants in both arms will be offered routine SoC and asked to complete validated QoL questionnaires at regular intervals (described above). In addition, those in the intervention arm will be offered the device-generated data collection platform (BD4QoL device *plus* QoL validated questionnaires *plus* counseling and physician contact triggered by the data generated by the platform [early intervention] *plus* a possible psychological effect of the whole activities in the interventional arm). A 2:1 randomization will be used (2/3 of subjects with BD4QoL platform versus 1/3 of subjects without). Participants randomized to the control arm will not receive the above-mentioned platform; they will fill in the same validated questionnaires on web-based instruments and will be followed up as per usual clinical practice.

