#### BD4QoL platform (intervention arm only)

2.5.4

The primary endpoint will be analyzed based on intention to treat. In addition to the criteria described in point 6.2.1, a study subject randomized in the intervention arm will be considered for the per-protocol analysis, if the BD4QoL platform is turned on for at least 70% of daily hours (non-sleep activity, as defined in **Supplementary Table 1**).

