#### Statistical plan

2.5.6

A comprehensive statistical plan will be prepared, discussed, and consented with the study team after data collection is completed and before the data analysis starts. The current plan is as follows: descriptive statistics will be generated for all clinical characteristics and outcome measures as appropriate (for continuous variables: sample size [n], mean, standard deviation, median, minimum, maximum, kurtosis, skewness; for categorical variables: frequency, percentage). All the analyzes will be performed using the ITT population and per-protocol. Missing data will be considered as lack of data. An analysis of missingness will be performed to understand whether there is relevant selection bias and appropriate methods to handle missing data will be applied according to the plausibility of the missingness mechanisms in the data.

The full sample size is expected to be accrued in an 18-month period. An interim analysis (only for checking patient number) will be performed after 12 months from the study start. If at least 50% of the planned population (≥210 subjects) have been randomized within the first 12 months of recruitment, the trial will continue with no modifications. Otherwise (randomized patients ≤ 209 patients in the first 12 months of study conduction), the BD4QoL Consortium will discuss, plan and agree strategies to foster patient recruitment, and eventually ask the funding Institution for a project extension. In case of any change in the clinical study protocol, a major amendment to the protocol will be submitted to the Ethical Committees of the participating sites.

All the analyzes, summaries, listings will be carried out using SAS statistical software (SAS version 9.4 of the SAS System, SAS Institute Inc., Cary, NC, USA). All statistical models will be fitted with SAS statistical software (SAS version 9.4 of the SAS System, SAS Institute Inc., Cary, NC, USA).

Sample size calculation was performed with PASS statistical software (PASS Sample Size 2020 - NCSS, LLC).

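### Table 3 and section 2.5.4 give incompatible per-protocol definitions, and Table 3's as-received rule could count intervention-arm never-users as controls

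*Protocol article*

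**What the plan says.** Table 3 (section 2.5.2) defines the per-protocol population as "All randomized participants completing at least two QoL questionnaires 6 months apart, as long as the study participant is disease-free". It sets no condition on platform use. It then fixes how members are assigned to groups: "Participants will be analyzed according to the intervention they actually received".

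Section 2.5.4 says that an intervention-arm participant "will be considered for the per-protocol analysis, if the BD4QoL platform is turned on for at least 70% of daily hours". It introduces this condition with "In addition to the criteria described in point 6.2.1". No point of that number appears in the article; the reference is presumably to the questionnaire criteria now in section 2.5.3.

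Three other statements bear on the point:

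- Section 2.2: "Participants randomized to the control arm will not receive the above-mentioned platform". Controls complete the same questionnaires through web-based instruments.
- Table 3 says that the ITT population, by randomised arm, "will be the primary population for the analysis of efficacy data". Section 2.5.4 repeats that the primary endpoint is analysed by intention to treat.
- Section 2.5.6: "All the analyzes will be performed using the ITT population and per-protocol".

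**The concern.** The two sections disagree on who belongs to the per-protocol set and on which group some members belong to. Table 3 also uses an as-treated assignment rule inside a population labelled per-protocol. In this trial that rule can act in only one direction, because no control can receive the platform. Any participant it reassigns goes from intervention to control.

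If people who never take up the platform tend to do worse, reassigning them lowers the intervention event rate and raises the control rate at once. The documents do not establish that link. The trial's own premise, that changes in activity and phone use can signal decline in quality of life (section 2.6.6), makes it plausible. Every analysis is to be run per-protocol beside ITT, so the ambiguity reaches the per-protocol version of each efficacy result. In an open-label trial the choice between two sets should not be left until data are seen.

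**Working it through.** **1. The two rules side by side.** All participants below have the required questionnaires and are disease-free.

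| Participant | Table 3 alone | With 2.5.4 |
|---|---|---|
| Control | In, as control | In, as control |
| Intervention, platform on at least 70% | In, as intervention | In, as intervention |
| Intervention, some use but below 70% | In, most naturally as intervention | Excluded |
| Intervention, never used | In, could be counted as control | Excluded |

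The rules differ in the last two rows. Only the last row can change who the controls are.

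**2. The plan's own figures (section 2.5.1).** The inputs are 20% versus 10%, one-sided alpha 0.05, 80% power and 2:1 allocation. The pooled normal-approximation formula gives 114 and 228, against the stated 112 and 224. Exact binomial power of the one-sided chi-squared test at 112/224 is 80.1%. For 20% drop-out, 112/0.8 = 140 and 224/0.8 = 280. The stated sizes are sound and are used below.

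**3. Effect of moving never-users when the platform does nothing.** Both randomised arms have the plan's 20% risk. The never-user fraction f and their risk q are assumptions; the documents give neither.

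- n = 224 × f
- User risk = (224 × 0.20 − n × q) / (224 − n)
- Control risk after the move = (112 × 0.20 + n × q) / (112 + n)

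*f = 20%, q = 30%:* n = 44.8.
- Users: (44.8 − 13.44)/179.2 = 31.36/179.2 = 17.5%
- Control: (22.4 + 13.44)/156.8 = 35.84/156.8 = 22.9%
- False benefit: 5.4 points. Of the control group, 44.8/156.8 = 29% would have been randomised to the platform.

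*f = 3%, q = 30%:* n = 6.72.
- Users: (44.8 − 2.016)/217.28 = 19.7%
- Control: (22.4 + 2.016)/118.72 = 20.6%
- False benefit: about 0.9 points

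*q = 20%, any f:* both risks stay at 20%, so there is no bias. The difference is n(q − 0.20)[1/(112 + n) + 1/(224 − n)], so it changes sign if never-users do better than 20%.

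**4. Chance of a one-sided significant result with no true effect** (exact binomial, f = 20%, counts rounded to 45 moved and 179 users):

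| q | Never-users moved to control | ITT |
|---|---|---|
| 20% | 5.2% | 5.1% |
| 25% | 15.6% | 5.1% |
| 30% | 34.4% | 5.1% |
| 35% | 58.6% | 5.1% |

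**5. Exclusion is not neutral either.** If the 20% at 30% risk are excluded rather than moved, the comparison is 20% versus 17.5%, a false benefit of 2.5 points.

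**The case against.** The strongest reply is that 2.5.4 is worded as an additional criterion. Read with Table 3, it requires the questionnaire condition plus 70% use, so never-users are out of the per-protocol set and nobody is moved. That reading is available. It leaves the as-received sentence with nothing to act on, and the protocol does not say which rule governs. The inconsistency stands; that anyone will in fact be moved does not.

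A reader might go further in three ways that the documents do not support:

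- **That participants who switch the app off early would also become controls.** Section 2.2 describes the intervention as the platform, counselling, triggered physician contact and a possible psychological effect. Someone who used it for a time received part of that, not the control condition. The clear case is never-use. Eligibility requires a suitable phone and willingness to use it for the study, so never-use may be uncommon.
- **That moving participants is always worse than excluding them, by some fixed factor.** That holds only if the same participants fall under both rules. Table 3 could move only never-users, whereas 2.5.4 excludes everyone below 70%. Moving 3% at 30% risk gives about 0.9 points; excluding 20% at 30% risk gives 2.5.
- **That non-use by itself creates a benefit.** It does so only if never-users have a worse prognosis.

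The primary result is also protected, since ITT by randomised arm is stated twice, and no passage lets a per-protocol result establish efficacy.

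**Conclusion.** The concern holds in a limited form. The protocol gives two per-protocol definitions that cannot both apply as written, and one contains an as-received rule that is either redundant or moves never-users from intervention to control. In the second case randomisation is broken, and the per-protocol result favours the platform if never-users do worse.

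The size rests on assumed inputs: 5.4 points for 20% never-users at 30% risk, about 0.9 points for 3% at 30% risk, and none at 20% risk. Against the 10-point target difference, the first would be material and the second small. The primary ITT analysis is not affected. This is a correction to a secondary analysis set, worth making because that set accompanies every analysis.

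**What to change.** - State one per-protocol definition and use it identically in Table 3 and section 2.5.4, with the platform-use condition in both or in neither. Removing the as-received sentence alone would not reconcile them: Table 3 would still admit a never-user whom 2.5.4 excludes.
- Replace the as-received sentence with a statement that participants are analysed in the arm to which they were randomised.
- Label any as-treated analysis separately as exploratory.
- Report platform non-use descriptively within the intervention arm.
- Correct the pointer to point 6.2.1 while editing.

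The cost is a few lines of text, with no new data or participants. One limitation remains: a use-based exclusion applied to one arm, if kept, still carries selection bias, so the per-protocol result should be read as supportive only.

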#### Questionnaires (both intervention and control arms)

2.5.3

For the primary endpoint, a randomized patient will be considered evaluable given that at least two QoL questionnaires have been completed with the following timing: timing between 2 questionnaires ≥ 6 months as long as the study participant is disease-free.

#### BD4QoL platform (intervention arm only)

2.5.4

The primary endpoint will be analyzed based on intention to treat. In addition to the criteria described in point 6.2.1, a study subject randomized in the intervention arm will be considered for the per-protocol analysis, if the BD4QoL platform is turned on for at least 70% of daily hours (non-sleep activity, as defined in **Supplementary Table 1**).

#### Data collection

2.5.5

At study entry, the following data will be collected and recorded in the electronic case report form (eCRF): date of signed informed consent, gender, marital status, education, date of primary tumor diagnosis, comorbidity (ACE27), baseline body mass index (BMI), age at primary tumor diagnosis, primary tumor site (International Classification of Diseases for Oncology, ICD-O code), HPV and/or p16 status (mandatory if primary tumor site = oropharynx), serum plasma Epstein-Barr Virus (EBV)-DNA (optional if primary tumor site = nasopharynx), EBER (EBV Encoded small RNAs) on tumor specimen (optional if primary tumor site = nasopharynx), Baseline (pre-treatment) cTNM staging^19^ (AJCC/UICC VIII edition), details about surgery, radiotherapy, systemic therapy, date of treatment completion.

At each follow-up, the following data will be collected and recorded in the eCRF: date of consultation, timing after treatment completion (first follow-up; +6 months; +12 months; +18 months; +24 months; other), BMI, disease status (recurrence; date of recurrence; site of recurrence: loco-regional and/or distant and/or second primary tumor), new non-cancer-related medical events [Medical Dictionary for Regulatory Activities (MedDRA)], grade of non-cancer-related medical events according to CTCAE (Common Terminology Criteria for Adverse Events) version 5.0, date of onset and resolution of non-cancer-related medical events, intervention for non-cancer-related medical events (no intervention; surgery; rehabilitation; medical intervention, if yes, to be specified according to Anatomical Therapeutic Chemical Classification System [ATC]; Psychological intervention; other).

#### Statistical plan

2.5.6

A comprehensive statistical plan will be prepared, discussed, and consented with the study team after data collection is completed and before the data analysis starts. The current plan is as follows: descriptive statistics will be generated for all clinical characteristics and outcome measures as appropriate (for continuous variables: sample size [n], mean, standard deviation, median, minimum, maximum, kurtosis, skewness; for categorical variables: frequency, percentage). All the analyzes will be performed using the ITT population and per-protocol. Missing data will be considered as lack of data. An analysis of missingness will be performed to understand whether there is relevant selection bias and appropriate methods to handle missing data will be applied according to the plausibility of the missingness mechanisms in the data.

The full sample size is expected to be accrued in an 18-month period. An interim analysis (only for checking patient number) will be performed after 12 months from the study start. If at least 50% of the planned population (≥210 subjects) have been randomized within the first 12 months of recruitment, the trial will continue with no modifications. Otherwise (randomized patients ≤ 209 patients in the first 12 months of study conduction), the BD4QoL Consortium will discuss, plan and agree strategies to foster patient recruitment, and eventually ask the funding Institution for a project extension. In case of any change in the clinical study protocol, a major amendment to the protocol will be submitted to the Ethical Committees of the participating sites.

All the analyzes, summaries, listings will be carried out using SAS statistical software (SAS version 9.4 of the SAS System, SAS Institute Inc., Cary, NC, USA). All statistical models will be fitted with SAS statistical software (SAS version 9.4 of the SAS System, SAS Institute Inc., Cary, NC, USA).

Sample size calculation was performed with PASS statistical software (PASS Sample Size 2020 - NCSS, LLC).

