**Figure 1 f1:**
[figure not shown]
Study design of the randomized controlled trial.

In this scenario, the 2:1 ratio was chosen for the following reasons: i) the study devices are deemed to be safe and able to provide timely monitoring of participants health status, thus 1) possibly improving their condition as compared to the control group and 2) minimizing the number of patients not exposed to this potential benefit; ii) the platform acts unobtrusively, and it favors contact with healthcare professional which is normally very well accepted and pursued by patients; moreover it is designed to allow for patients’ empowerment; iii) we anticipate that costs associated with SoC not supported with the BD4QoL platform will be superior because subjects randomized in the intervention arm are deemed to experience less adverse events than controls. In this context, a cost-effectiveness analysis is planned as an exploratory endpoint (**Table 2**).

As stated by Palmer et al., favoring the experimental therapy is warranted in trials of potentially significant public health benefit (21). Unequal allocation schemes can improve recruitment and partially satisfy the individual ethics criterion (the study participants have a higher probability of being randomized in the intervention arm than in control one). They can also be useful if widespread knowledge about the control therapy already exists and if more understanding is desired about the new treatment.

The randomization procedure will be web-based, centralized, computerized (software-generated randomization list using RedCap web-based platform) (22, 23). Local research teams will be blinded to the randomization list (local people designated to the randomization procedure will not know the randomization list, but clinical investigators will not be blinded to the outcome of the randomization). The biostatistician doing the analysis of the trial will be blinded to the list as well until the statistical analysis plan, previously defined, is signed.

The EORTC QLQ-C30 (4), EORTC QLQ-HN43 (6), EQ-5D-5L (8), and CBI-B (11) evaluations will be performed at 0-, 6-, 12-, 18-, 24-month from randomization. The time zero is considered to be the date of randomization. The scores of the EORTC QLQ instruments [as defined in (13, 14)] will be compared to the respective scores of the previous study time-point.

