#### QoL questionnaire data entry and data retrieval

2.6.5

The completion of study questionnaires will be performed the same day of the outpatient consultation ± 2 weeks, using web-based forms available at participating Centers or remotely, e.g., through tablets or personal computers (PC). QoL data will be accessible to clinical investigators, and to patients whenever asked.

If the subject does not go to the clinical institution for an outpatient visit or is not being seen every 6 months (± 2 weeks), the investigators will contact the patient by phone asking to fill in the requested questionnaires through the same web-based forms. The PoC dashboard will notify the investigators with an alert 2 weeks after the “due date” if any questionnaire has been initialized but has not been completed.

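### Section 2.5.6 has the analysis plan written and agreed only after data collection, by a study team that may include investigators who know arm and outcome for their own patients

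*Protocol article*

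**What the plan says.** On timing, section 2.5.6 (Statistical plan) says the comprehensive plan will be drawn up and agreed with the study team "after data collection is completed and before the data analysis starts". Preparation as well as sign-off therefore comes after the last outcome. The same section gives a short current plan, and on missing data it says that "appropriate methods to handle missing data will be applied according to the plausibility of the missingness mechanisms in the data".

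On masking, section 2.2 (Study design) describes a "two-arm, randomized (2:1 ratio), open-label, superiority trial". The text after Figure 1 adds that "clinical investigators will not be blinded to the outcome of the randomization", while the analysing biostatistician "will be blinded to the list as well until the statistical analysis plan, previously defined, is signed".

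On access to the endpoint, section 2.6.5 states: "QoL data will be accessible to clinical investigators, and to patients whenever asked". Section 2.7.2 limits clinical investigators to patients recruited at their own centre. Sections 2.2 and 2.6.7 end a patient's participation once a drop of 10 points or more is detected.

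**The concern.** Finalising a plan late does little harm if nobody involved knows outcomes by arm. Here some of those involved may know them. An investigator at a recruiting centre knows each local patient's arm, can read the scores, and knows who left the study because of a primary event. If such investigators belong to the study team that agrees the plan, they do so with that knowledge.

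This matters because the protocol has not closed every choice that affects the primary result. A plan signed before follow-up outcomes are reviewed would close them with no suspicion attached. A plan agreed after data collection cannot show from its date alone that the choices were independent of the results. At stake is how far the one-sided 5% level in section 2.5.1 can be trusted in a trial with a subjective endpoint and no masking of patients or clinicians.

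**Working it through.** **1. The stated design figures.** Section 2.5.1 assumes 20% versus 10%, 2:1 allocation, one-sided alpha 0.05 and 80% power. With the pooled formula without continuity correction, k = 2 and p̄ = (0.20 + 2 × 0.10)/3 = 0.1333:

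n(control) = [1.645 × √(1.5 × 0.1333 × 0.8667) + 0.842 × √(0.16 + 0.09/2)]² / 0.10² ≈ 114, so 228 for the intervention arm.

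The article has 112 and 224, where the same formula gives 79.5% power. Drop-out: 112/0.8 = 140 and 224/0.8 = 280, total 420. The figures are reproduced within rounding. Nothing in this point changes them; they only supply the 5% level in question.

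**2. Who knows what when the plan is agreed.**
- Clinical investigators: allocation (2.2), scores (2.6.5) and primary events (2.2, 2.6.7), for their own centre only (2.7.2).
- Analysing biostatistician: not the randomization list until signature (2.2).
- Nonclinical investigators: pseudonymized data, clinical and device-generated (2.7.2). Continuous app monitoring exists in the intervention arm only (Table 4), so the presence of device data would reveal the arm without the list. The article does not say the statistician uses these data before signing, nor that this is barred.
- The look at 12 months counts randomized patients only (2.5.6).
- No section describes a pooled comparison by arm before signature, and none forbids it.

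**3. What is still to be settled.**
- *Analysis set.* Table 3 and section 2.5.4 make ITT primary. Section 2.5.3 counts a patient as evaluable for the primary endpoint only with two questionnaires at least 6 months apart while disease-free.
- *Reference score.* Section 2.2 compares with the previous time-point, and section 2.6.7 refers to two questionnaires 6 months apart. The abstract allows deterioration at any point, and Table 1 speaks of at least two visits.
- *Missing data.* The method depends on an assessment of missingness made on the data (2.5.6).

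The first two are nominally fixed but contradicted elsewhere; the third is not fixed.

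**4. What selection could do: an illustration.** The article gives no inputs for this, so all are assumed: no treatment effect, 140 and 280 patients, mean 70, SD 20, scores in steps of 100/12, within-patient correlation 0.5 to 0.85, drop-out 20% to 30% unrelated to arm, 4,000 simulated trials per setting. Eight analyses were compared: two reference scores (baseline or previous visit) by four rules for analysis set and missing data.
- Each analysis alone: one-sided error 0.042 to 0.056.
- The most favourable of the eight, picked with full sight of results by arm: 0.142 to 0.155.
- A choice made without knowledge of arm: near 0.05, because under the null the arm labels carry no information about which analysis is favoured.

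The middle line is a worst case that the article does not describe. The last line is what the safeguards aim at. The actual process lies between them at a point the article does not determine.

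**The case against.** The strongest defence is that the sequence is acceptable as written: data collected, plan agreed, plan signed, list opened, analysis run. The biostatistician is blinded throughout, ITT and the previous time-point are named, and leaving detailed missing-data methods to the SAP is normal. The wording in section 2.2, "until the statistical analysis plan, previously defined, is signed", can be read as defined before signature, which fits section 2.5.6.

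Much of this stands. A reader might infer that the plan will be chosen with results by arm on view, or that the 5% level is lost. The documents do not support either reading. Investigators see individual patients at one centre, no pooled comparison by arm is described, and the plan precedes the analysis. Nor can the whole study team be called unblinded: the article does not define the team, and the biostatistician is blinded. It would also be wrong to call the analysis set and reference score simply open. The wording of section 2.2 is at most loose beside section 2.5.6, not a proven contradiction.

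What the defence does not answer is the stated timing. Section 2.5.6 does more than leave content to the SAP: it fixes preparation after the last outcome and requires the study team's agreement. Blinding the statistician does not blind the others who agree the plan. The inconsistencies in step 3 have to be resolved somewhere, and as written they would be resolved then.

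**Conclusion.** The point holds as a weakness in timing and in safeguards. The plan is to be prepared and agreed after all outcomes are in. The team may include investigators who know arm and outcome for part of the sample, while the analysis set, the reference score and the missing-data method still need a decision or a reconciliation. Protection of the one-sided 5% level is weakened, not removed.

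The size cannot be derived from the article. The 0.14 to 0.16 in the illustration is not an estimate for this trial: it rests on assumed inputs and on full sight of results by arm. The conclusion rests on one inference, that the study team includes clinical investigators, which the article neither states nor rules out. The change is worth making because it is cheap and because an early signature cannot be recreated after data collection ends.

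**What to change.** Amend section 2.5.6 as follows:
- The SAP is written by the blinded statistician, and signed and dated before follow-up outcome data are reviewed. If follow-up has begun, this is done immediately, and in any case before data collection ends.
- It fixes the reference score for the 10-point drop, the primary missing-data method, and whether the primary analysis uses all randomized patients or the evaluable set.
- No summaries by arm are produced before signature.
- Later changes are dated amendments made blind to arm.

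Align section 2.2 so that both sections describe the same order of events.

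Cost: the same document, written earlier, with later changes needing a dated amendment. The sample size is unaffected.
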